## Abstract

**Background:**

Shared decision making (SDM) in breast cancer care improves outcomes, but it is not routinely implemented. Results from the What Matters Most trial demonstrated that early-stage breast cancer surgery conversation aids, when used by surgeons after brief training, improved SDM and patient-reported outcomes. Trial surgeons and patients both encouraged using the conversation aids in routine care. We will develop and evaluate an online learning collaborative, called the SHared decision making Adoption Implementation Resource (SHAIR) Collaborative, to promote early-stage breast cancer surgery SDM by implementing the conversation aids into routine preoperative care. Learning collaboratives are known to be effective for quality improvement in clinical care, but no breast cancer learning collaborative currently exists.

Our specific aims are to (1) provide the SHAIR Collaborative resources to clinical sites to use with eligible patients, (2) examine the relationship between the use of the SHAIR Collaborative resources and patient reach, and (3) promote the emergence of a sustained learning collaborative in this clinical field, building on a partnership with the American Society of Breast Surgeons (ASBrS).

**Methods:**

We will conduct a two-phased implementation project: phase 1 pilot at five sites and phase 2 scale up at up to an additional 32 clinical sites across North America. The SHAIR Collaborative online platform will offer free access to conversation aids, training videos, electronic health record and patient portal integration guidance, a feedback dashboard, webinars, support center, and forum. We will use RE-AIM for data collection and evaluation. Our primary outcome is patient reach. Secondary data will include (1) patient-reported data from an optional, anonymous online survey, (2) number of active sites and interviews with site champions, (3) Normalization MeAsure Development questionnaire data from phase 1 sites, adaptations data utilizing the Framework for Reporting Adaptations and Modifications-Extended/-Implementation Strategies, and tracking implementation facilitating factors, and (4) progress on sustainability strategy and plans with ASBrS.

**Discussion:**

The SHAIR Collaborative will reach early-stage breast cancer patients across North America, evaluate patient-reported outcomes, engage up to 37 active sites, and potentially inform engagement factors affecting implementation success and may be sustained by ASBrS.

**Supplementary Information:**

The online version contains supplementary material available at 10.1186/s43058-023-00453-z.

Contributions to the literature
• The SHAIR Collaborative is a novel breast cancer learning collaborative engaging breast cancer care teams across North America in implementing shared decision making by using two variations of an early-stage breast cancer conversation aid.• Our evaluation plan, guided by the Reach Effectiveness-Adoption Implementation Maintenance framework, uses multiple established frameworks and will be useful for informing other implementation efforts.• Implementation of the SHAIR Collaborative is guided by a community-based participatory research approach, involving all stakeholders in an effort to promote sustainability.

## Background

Early-stage breast cancer surgery treatment is preference-sensitive and therefore warrants shared decision making [1]. However, only 44 to 51% of patients with early-stage breast cancer achieve the degree of participation in decision making they desire, and many report poor knowledge about breast cancer surgery options [2–7]. Shared decision making in breast cancer care is important and improves patient outcomes like knowledge and decision regret, but it is not routinely implemented due to barriers like lack of appropriate training, access to evidence-based conversation aids, and the potential to disrupt workflows [8–10]. Patients and clinical teams alike desire sustained implementation of shared decision making in breast cancer care [9, 11].

The What Matters Most randomized controlled trial provided early-stage breast cancer patients and their surgeons with either a text-based or picture-enhanced with simpler words encounter-based conversation aid (Option Grid™ or Picture Option Grid) to facilitate shared decision making for this surgery decision [12]. The results of the What Matters Most trial demonstrate that the conversation aids, when used by surgeons after a brief training, led to significant increases in observed and patient-reported shared decision making, and improved patient-reported outcomes, including higher knowledge, lower decision regret, and perception of receiving more coordinated care [12, 13]. Picture Option Grid, as predicted, had a stronger impact among patients with lower health literacy and lower socioeconomic position. Interviews with What Matters Most surgeons and patients showed that both would encourage and promote the use of the conversation aids in future breast cancer care [11]. Intervention surgeons reported that the conversation aids did not lengthen consultation time and enhanced their usual care after using it a few times [11]. One review and other studies that have evaluated Option Grids have reported similar results [14–17]. Further evidence has recently been published showing the superiority of brief encounter-based tools [18].

Given that Option Grid and Picture Option Grid for early-stage breast cancer improve patient-reported outcomes and the conversation aids are desired in breast cancer care, we are implementing a shared decision making strategy that was formally tested and demonstrated effectiveness in the context of the What Matters Most trial [11, 12]. The effective shared decision making strategy included the two conversation aids and a brief training module for participating breast surgeons. In this implementation protocol, we augment the strategy by embedding it in an online learning collaborative. The learning collaborative approach is based on Wenger’s community of practice model and has been frequently adopted in healthcare quality improvement programs [19]. There is a well-established body of evidence to support the use of learning collaboratives, and a systematic review found that these types of collaboratives lead to significant improvements in clinical processes and patient outcomes [20, 21]. The SHared decision making Adoption and Implementation Resource (SHAIR) Collaborative will be hosted on an open-access website for breast surgeons and will include (1) free access to the early-stage breast cancer Option Grid and Picture Option Grid conversation aids in multiple languages, (2) brief shared decision making training, (3) implementation support through online and recorded webinars, implementation checklists, electronic health record and telehealth integration guidance, and other appropriate support materials, and (4) a feedback dashboard to anonymously share patient-reported outcomes from participating sites [22, 23].

Our specific aims are to (1) provide the SHAIR Collaborative and all of its resources to clinical sites and its eligible patients, (2) examine the relationship between access and use of the SHAIR Collaborative offerings and the success of the implementation, and (3) create a sustained learning collaborative in this clinical field to support ongoing use of shared decision making.

## Design and methods

All title/abstract, introduction, and methods have been reviewed utilizing StaRI, the Standards for Reporting Implementation studies (Additional file 1: Appendix 1) [24].

### Design and theoretical basis

Our theoretical basis is Rogers’ Diffusion of Innovation Theory [25]. Diffusion occurs through a five-step process, including knowledge/awareness of the innovation (i.e., early-stage breast cancer conversation aids), persuasion, decision to innovate, implementation of the innovation, and continuation of the innovation. The social system is a key element of diffusion of innovation [25, 26]. The development of an online learning collaborative will provide a foundation to support this element. We will target “early adopters”, but overall rely on developing an “early majority” of adopters, as those who adopt innovations sooner than most, but require evidence of effectiveness prior to adoption. We are targeting several stages of adoption with the learning collaborative: (1) dissemination of shared decision making utilizing evidence-based conversation aids, (2) implementation of the conversation aids in diverse clinics across North America by utilizing an online learning collaborative approach, and (3) potential sustainability/continuation of the learning collaborative [27].

Since the text-based and picture-enhanced conversation aids were found to be effective in improving shared decision making compared to usual care in a comparative effectiveness trial, we outline below our design for an implementation project to broadly implement the conversation aids.

We will conduct a two-phased implementation project: phase 1 is to pilot our implementation approach, and phase 2 is to scale up the implementation. In phase 1, we will design and develop the implementation platform in conjunction with our project stakeholders. We will then test the implementation platform and approach at our phase 1 pilot sites across the USA, who are our “early adopters” (four out of five phase 1 sites were participating sites in the comparative effectiveness trial). Next, we will refine the approach and prepare for phase 2. In phase 2, we will broadly implement the platform in additional clinical sites across the USA, Mexico, and Canada. Phase 2 sites are the “early majority” of adopters and will learn from phase 1 sites’ “early adopters”. Throughout both phases, we will explore features of sustainable implementation. These sites and our stakeholders will become the SHAIR Collaborative, an online learning collaborative committed to implementing shared decision making for patients with early-stage breast cancer.

### Settings

Phase 1 settings will include five academic medical centers: Dartmouth-Hitchcock Medical Center (Lebanon, NH), Washington University in St. Louis (St. Louis, MO), Montefiore Medical Center (Bronx, NY), Bellevue Hospital (New York, NY), and the University of Miami (Miami, FL). We selected these sites for initial testing of the implementation platform to ensure broad representation of patient demographics and underlying interest in implementing shared decision making in their practices. Four of the five phase 1 sites participated in the What Matters Most trial [12].

Phase 2 settings will include up to an additional 32 clinical sites: single clinician private practices, multi-clinician private practices, local and regional hospitals, and academic medical centers. Phase 2 sites will be located in North America. We recruited an initial set of phase 2 sites when applying for funding and will finalize the set of sites prior to the start of phase 2. Sites will be eligible if they have practicing breast cancer surgeons who treat patients with early-stage breast cancer. Phase 2 sites will receive a small honorarium to cover costs associated with the minor research activities of participation in the SHAIR Collaborative. We will allow for additional sites to join the SHAIR Collaborative as feasible.

### SHAIR Collaborative platform and offerings

In phase 1, we will design the implementation platform which will include key offerings, all centered around supporting implementation of shared decision making for early-stage breast cancer patients. The SHAIR offerings are based on our assessment of positive implementation factors reported to date from previous implementation experience [12, 28]. Adaptations to the resources/offerings and implementation strategy will be guided by project stakeholders and made as necessary. All offerings will be available via the open-access website.*Free and direct access to the Option Grid conversation aids*. Produced by EBSCO Health, these conversation aids are continuously updated and offered in perpetuity free of charge [29]. A dedicated website will ensure direct open access to the Early-Stage Breast Cancer Surgery Option Grid and Picture Option Grid, as well as downloadable PDF versions in multiple languages (English, Spanish, Mandarin Chinese). We will obtain certified translations of the conversation aids for additional languages as requested. We will encourage the use of interpreters and interpretation technology where patients speak other languages that Option Grid is not currently offered in.*Training and instructional videos*. We will develop a set of short training videos that will be designed to train clinicians in shared decision making and implementation and support the SHAIR Collaborative. We have planned for an initial set which includes an introduction to the SHAIR Collaborative, introduction to shared decision making, communicating shared decision making using the three-talk model [30], using Option Grids as an encounter-based conversation aid in clinical practice, and how to implement conversation aids in diverse clinical settings. This list of videos and deciding on future instructional videos will be refined and added to based on stakeholder input.*Integration guides*. Our experience indicates that electronic health record (EHR) integration of conversation aids is complex, requiring clinical leadership, institutional prioritization, and funding for and access to EHR integration experts [28]. In collaboration with the expertise of EBSCO Health and the project’s other stakeholders, we will develop a downloadable PDF guide to integrating the Option Grids and Picture Option Grids into the EHR. Rapid uptake of telehealth as a result of the COVID-19 pandemic has transformed the use of patient portals to send materials to patients ahead of their encounters [23]. We will provide downloadable PDF guides on how to embed the conversation aids into workflow processes so that patients can be given the conversation aids at the appropriate time, allowing for context-sensitive delivery of the conversation aids.*Feedback dashboard*. Phase 1 and phase 2 sites will provide monthly data on patient reach. We will also collect optional, anonymous online patient surveys from participating sites. A summary of these data will be displayed via a feedback dashboard.*Webinars*. We will host live, recorded SHAIR Collaborative webinars starting in phase 2. The content, length, format, platform, and frequency of the webinars will be decided and refined by project stakeholders. Recordings and relevant materials from these webinars will be available to SHAIR Collaborative members.*Support center and forum*. Members of the Collaborative will be able to issue support requests and engage with other Collaborative members via email and website support forum. There will also be a section of the website dedicated to frequently asked questions.

### Site onboarding and training

We will ask surgeons at each site to view the initial set of training videos available on the platform (component 2 above) before beginning implementation at their site. We will also offer virtual site initiation visits (SIVs) to all phase 1 and phase 2 sites but will only require them for phase 1 sites. We will invite surgeons, clinic and administrative staff, and any other appropriate clinical or non-clinical contacts to the SIVs based on site needs. At minimum, each SIV will include an introduction of SHAIR and training (if needed) and discussion regarding the site’s implementation strategy. Lastly, we will provide an implementation checklist to phase 2 sites based on guidance and best practices from phase 1 sites.

### Data collection and evaluation

We will use the RE-AIM framework to guide our data collection and evaluation of this implementation project. RE-AIM addresses reach, effectiveness, adoption, implementation, and maintenance [31].

#### Reach

##### Data collection

Our primary outcome is patient reach, which is defined as the number of patients who are given the opportunity to use one of the conversation aids over the number of eligible patients, by site. Surgeons using the conversation aids at each site will determine patient eligibility based on clinical judgment. We will determine patient reach for each site on a monthly basis using the following data:Reported uses of the conversation aids—We will email each site monthly to request data and notes for the previous month regarding patient reach. Other uses of the conversation aids can include using paper copies, sending links or PDFs to patients by email, patient portal, EHR, or other distribution methods.From our experience, we anticipate that paper versions will be used only once with patients [11]. However, we realize a patient may be given multiple copies throughout their care and/or for others to view (family members, friends, caregivers). While this may occur, we do not anticipate our sites to regularly provide multiple paper copies of an Option Grid/Picture Option Grid. In the instance multiple copies are given, we will work with each site to try and get as accurate of count as possible.Online access to conversation aids via platform—The SHAIR Collaborative website is able to track the downloads of the conversation aids or clicks out to the linked EBSCO website for the interactive tools. Downloads will be tracked and reported on a monthly basis.

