##### Evaluation

Reported patient reach data and site-specific online accesses of the conversation aids will be counted for each site monthly. We will calculate patient reach as the percentage of eligible patients receiving the Option Grid or Picture Option Grid. We will report this overall and by site for sites with sufficient data. In the patient reach email response from sites, any details given regarding barriers and facilitators to patient reach will be noted and responded to, as appropriate.

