##### Evaluation

We will calculate descriptive statistics summarizing the NoMAD survey results for each phase 1 site at the conclusion of the implementation period.

Separately, we will use the factors shown from Table 1 as variables in a linear regression analysis to explore which factors might be associated with high levels of patient reach (clinical championship, team engagement, communications engagement etc.) and therefore might predict future patient reach. For these regressions, patient reach will be the dependent variable and each implementation factor will be an independent variable. We will assess each item at the site level so that “site” will be the unit of analysis. We will control for patient demographics and other potential sources of site heterogeneity, if possible.

Additionally, we will conduct mixed-effects linear or logistic regression analyses to examine the association between these implementation factors and our patient-reported outcomes. We will conduct an analysis for each outcome while controlling for patient demographics as fixed effects. For this analysis, “patient” will be the unit of analysis but we will account for clustering at the site level as a random effect.

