### Data management

Patient reach data and implementation facilitating data will be tracked via spreadsheets and stored in a shared project folder. Survey data will be stored in the Dartmouth Qualtrics database, a HIPAA-compliant web-based data management system. Dartmouth project staff will not have access to the EHRs at any participating phase 1 or phase 2 sites. Our database management system is designed to comply with the ICH Good Clinical Practice guidelines. For statistical analysis, data will be downloaded and stored on an encrypted hard drive owned by Dartmouth College.

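### The surgeons who use the aids set the denominator of patient reach by judgment, with no common criterion and no independent count, so suitable patients not offered an aid can fall out of it unnoticed

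*Protocol article*

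**What the plan says.** The Reach section (Data collection) gives the primary outcome as a ratio, "defined as the number of patients who are given the opportunity to use one of the conversation aids over the number of eligible patients, by" (the unit named there is the site). The next sentence says who fills the denominator: "Surgeons using the conversation aids at each site will determine patient eligibility based on clinical judgment". The Evaluation part of the same section repeats the ratio: "We will calculate patient reach as the percentage of eligible patients receiving the Option Grid or Picture Option Grid".

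Two data sources are named. One is self-report: "We will email each site monthly to request data and notes for the previous month regarding patient reach". The other is the website: "Downloads will be tracked and reported on a monthly basis", together with clicks through to the interactive tools. Data management adds that "Dartmouth project staff will not have access to the EHRs at any participating phase 1 or phase 2 sites".

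Reach is then used as an outcome in two models. The Adoption section (Evaluation) regresses site-level reach on how connected members of the collaborative are. The Implementation section (Evaluation) relates it to the Table 1 factors, with site as the unit: "For these regressions, patient reach will be the dependent variable and each implementation factor will be an independent variable".

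Settings allows solo practices, multi-clinician practices, hospitals and academic centers. A site qualifies on its caseload: "Sites will be eligible if they have practicing breast cancer surgeons who treat patients with early-stage breast cancer". No sentence requires every surgeon at a site to use the aids.

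**The concern.** A proportion describes uptake properly only if its denominator is fixed without regard to its numerator. Here the people who decide whether to offer an aid also decide whether the patient counts as eligible, and clinical judgment is the only stated standard. A suitable patient who was not offered an aid can be classed as ineligible, and nothing in the reported data would show it.

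There is a second possible route. Read literally, only surgeons who use the aids classify patients. At a site where some surgeons do not use them, the article does not say how those surgeons' patients enter a ratio that is defined by site.

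Two things are at stake. The first is the level of the primary outcome, overall and by site. The second is comparability: if surgeons at different sites apply different thresholds, reach can differ between sites for reasons unrelated to implementation, and both site-level regressions inherit that difference. No later analysis can repair this if the missing counts were never collected.

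**Working it through.** **Figures in the plan.** The article states no expected reach, sample size or power for this outcome, so there is no figure to reproduce. What can be checked is the direction of the error and how large it would be over a range of assumed inputs.

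**Sources compared.**
- Monthly email: reported by the site; it is the only source that can carry the denominator.
- Website downloads and clicks: evidence of use, so numerator only.
- Site health records: closed to project staff.

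No source checks the denominator from outside the site.

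**Route 1: suitable patients not offered an aid are judged ineligible.** Let R be true reach among suitable patients and f the share of suitable, not-offered patients who are classed as ineligible. Both are assumptions. Then

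reported reach = R / [R + (1 − R)(1 − f)].

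The term in square brackets is at most 1, so reported reach is never below R. For R = 0.40 and f = 0.50: 0.40 / (0.40 + 0.60 × 0.50) = 0.40 / 0.70 = 57.1%.

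| True reach R | f = 10% | f = 25% | f = 50% | f = 75% |
|---|---|---|---|---|
| 20% | 21.7% | 25.0% | 33.3% | 50.0% |
| 40% | 42.6% | 47.1% | 57.1% | 72.7% |
| 60% | 62.5% | 66.7% | 75.0% | 85.7% |
| 80% | 81.6% | 84.2% | 88.9% | 94.1% |

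**Route 2: patients of non-using surgeons are not counted.** Let s be the share of the site's eligible patients seen by surgeons who use the aids, and u the reach among those patients. Site-wide reach is s × u, but u is reported. With assumed s = 50% and u = 80%, site-wide reach is 0.50 × 0.80 = 40% and the reported figure is 80%. With s = 75% it is 0.75 × 0.80 = 60%, against 80% reported. This route exists only where some surgeons at a site do not use the aids and their patients are left out.

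**The opposite error.** If patients with no real surgical choice are counted as eligible, adding a share e to the denominator, reported reach is R / (1 + e). For R = 40% this gives 0.40 / 1.10 = 36.4% at e = 10% and 0.40 / 1.25 = 32% at e = 25%.

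**Between sites.** Two sites with the same true reach of 40%, one with f = 10% and one with f = 50%, would report 42.6% and 57.1%. That gap of about 15 points has nothing to do with implementation. It biases a regression coefficient if f is related to the factor being studied.

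**The case against.** The strongest reply is that judgment belongs in this denominator. The aids are meant for a preference-sensitive choice, and whether a patient has that choice is a clinical question. Excluding patients who do not have it is legitimate and causes no bias. A denominator of all early-stage consultations would include them, lower reach by a case mix that differs between sites, and change what is being estimated. This stands, and it is why that count should be reported beside the judged-eligible figure and not replace it.

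Several stronger readings are tempting but not supported:

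- A reader might infer that eligibility is judged in the knowledge of whether an aid was given. The article does not say when eligibility is judged or who compiles the monthly count, and it describes materials being sent before the visit.
- A reader might infer that reach is certainly inflated, or driven toward 100%. The article gives no information on f, values near 100% need f near 1, and the error can also run downward.
- A reader might infer that patients of non-using surgeons are definitely excluded. The phrase about surgeons using the aids may simply mean the participating surgeons. The monthly request goes to the site, training is asked of surgeons at each site without restriction, and the question cannot arise in a solo practice.
- A reader might infer that partial uptake within a site would be invisible. Team and champion engagement are rated quarterly, barriers are noted from monthly replies, and champions are interviewed. These give other views of uptake, though none repairs the denominator.

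On weight, the project has no control arm, the article states no test or threshold on reach, and the regression on the Table 1 factors is exploratory. A condensed article may also leave operational eligibility wording to a fuller document. That does not dispose of the point, because the article does state the rule and who applies it.

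**Conclusion.** The concern holds in a limited form. As written, the denominator of the primary outcome depends on the people who decide whether to offer the aid, with no common criterion and no independent count. Losing suitable, not-offered patients from it can only raise reported reach, and the data as planned could not separate legitimate from convenient exclusion.

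The size cannot be derived from the documents. Under assumed values, the inflation at a true reach of 40% runs from 2.6 points (f = 10%) to 32.7 points (f = 75%). The effect on the regressions is conditional: it requires the misclassification to differ between sites in a way related to the factor studied, which the documents neither show nor exclude. The omission of non-using surgeons' patients is a possible reading, not a stated rule.

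This is a should-fix: a cheap improvement to the only primary outcome, not a flaw that invalidates the project.

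**What to change.** 1. Write one common description of an eligible patient and apply it to all surgeons at a site, whether or not they use the aids.
2. In the monthly email, also ask each site for (a) the total number of new early-stage breast cancer patients seen for surgical consultation across all surgeons, counted regardless of whether an aid was given, and (b) the number judged ineligible.
3. Report reach on both denominators: all such consultations, and those judged eligible.
4. Repeat both site-level regressions with the all-consultations denominator as a sensitivity analysis.

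If every patient judged eligible is truly suitable, and only suitable patients are offered an aid, the two figures bracket true reach. With the assumed values used above (R = 40%, f = 50%, e = 25%), they would be 57.1% and 32% around a true 40%. The count of patients judged ineligible also shows how far exclusion practice differs between sites.

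The cost is a slightly larger monthly task for sites, which matters because the article itself names the engagement of busy clinicians as a limitation. The all-consultations figure will also be lower and will include some patients with no real surgical choice, so it needs that caveat wherever it is shown. Project staff need no access to site records, and surgeons keep full discretion over whom they offer an aid.

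### The primary outcome, patient reach, is defined per patient, but website downloads and click-outs with no stated link to patients are named among the data that determine it

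*Protocol article*

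**What the plan says.** The Reach section (Data collection) of the protocol article defines the primary outcome as "the number of patients who are given the opportunity to use one of the conversation aids over the number of eligible patients, by site". It continues: "We will determine patient reach for each site on a monthly basis using the following data". Two sources follow.

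- **Site reports:** "Reported uses of the conversation aids—We will email each site monthly to request data and notes for the previous month regarding patient reach". The text beneath covers paper copies and links or PDFs sent by email, patient portal or EHR.
- **Online access:** the SHAIR Collaborative "website is able to track the downloads of the conversation aids or clicks out to the linked EBSCO website", with downloads tallied monthly.

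The Reach section (Evaluation) pairs the two again: "Reported patient reach data and site-specific online accesses of the conversation aids will be counted for each site monthly". The next sentence returns to patients: "We will calculate patient reach as the percentage of eligible patients receiving the Option Grid or Picture Option Grid".

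The platform section adds: "All offerings will be available via the open-access website". The only handling of multiple counts is a best-effort correction in the text on paper copies.

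Reach is the dependent variable in two planned analyses: the regression on social interconnectedness (Adoption, Evaluation) and the regressions on the Table 1 factors (Implementation, Evaluation). One Table 1 factor, website engagement, is scored Yes when a site downloads something from the website or comments there. Another rates progress in EHR, telehealth or portal integration.

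**The concern.** The definition counts patients, while one of the two sources named as determining it counts events. No rule links a download or click to a patient. The sources also overlap by design. A patient sent a link belongs in the site report, and if the link leads through the project website, that patient may also generate an access. In the other direction, a clinic may download a PDF once and print it for many patients. On an open-access site, staff, relatives or people outside the site's eligible group may also generate accesses.

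The size and direction of any error would therefore depend on how a site distributes the aids. That matters for comparing sites, and for the stated aim of relating use of the collaborative's resources to reach. A difference in distribution route could pass for a difference in reach, and integration progress could look like a driver of it. Downloads raise a further problem, because the same event can enter both the outcome and a predictor.

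The numerator is also worded loosely. It appears as patients offered an aid, as uses of an aid, and as patients receiving one. A site answering a monthly email could take these differently.

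**Working it through.** The article gives no reach target, sample size or expected number of accesses, so there is no figure to reproduce. The check uses the definitions plus simple arithmetic on assumed values.

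**Notation, per site and month.** E = eligible patients; R = patients the site reports as given or sent an aid; D = website accesses (downloads plus click-outs).

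- Patient count from site reports: reach = R/E, at most 100% if each eligible patient is counted once.
- Both counts added without de-duplication: (R + D)/E. This exceeds 100% when D > E − R, that is, when accesses per reported patient exceed (E − R)/R.

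**Assumed values.** E = 20; R = 10, 14 or 18; accesses per reported patient d = 0, 0.5 or 1, so D = d × R.

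| R | d = 0: R/E | d = 0.5: (R + D)/E | d = 1: (R + D)/E | Exceeds 100% when |
|---|---|---|---|---|
| 10 | 10/20 = 50% | 15/20 = 75% | 20/20 = 100% | D > 10 (d > 1.00) |
| 14 | 14/20 = 70% | 21/20 = 105% | 28/20 = 140% | D > 6 (d > 0.43) |
| 18 | 18/20 = 90% | 27/20 = 135% | 36/20 = 180% | D > 2 (d > 0.11) |

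The higher the true reach, the fewer accesses it takes to pass 100%.

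**Distribution route.** Take two sites that each give an aid to 14 of 20 eligible patients. One uses paper and has no accesses; the other sends links and has 0.5 accesses per patient. Under addition they show 70% and 105%, a gap of 35 percentage points with no difference in patients reached.

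**Opposite direction.** If one clinic download is printed for 10 patients, the access count is 1. Read as patients, that would be 1/20 = 5% where the true figure is 10/20 = 50%. Accesses can therefore understate as well as overstate.

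**Same event on both sides.** Take two sites with R = 10 and E = 20. The first has no downloads or comments, so website engagement is No. The second has 5 downloads, so it is Yes. From site reports both have 50%. Under addition the second has 15/20 = 75%. The regression would see a difference of 25 percentage points that comes only from the downloads.

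**The case against.** The strongest reply is that the article never says the counts are added. A reader might infer that reach is not a proportion of patients, or that the plan's reach will exceed 100%. The document does not support either as fact. It defines reach twice as a share of eligible patients, and the Evaluation text names reported reach data and online accesses as two quantities. Online accesses could be meant as a cross-check or a separate tally. The percentages above are conditional on addition and use assumed inputs. This part of the reply stands.

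A reader might also infer three competing outcomes from the three wordings. That goes too far. Being offered an aid and receiving one both describe provision by the site, and the text under the reported-uses label describes distribution. The wording needs tidying, but it does not show three different measures.

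Nor does open access show that accesses cannot be assigned to sites: the article plans site-specific counts, although it does not describe how. The text on multiple paper copies shows an intent to count patients.

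Finally, an article may leave a combining rule to the full protocol or analysis plan, so the absence of that rule is not itself the point. What remains is what the article states: a per-patient definition and, directly after it, an event count named as data that determine it. A rule elsewhere would have to undo that statement, not just add detail.

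**Conclusion.** The concern holds in a limited form. The primary outcome is defined per patient, yet downloads and click-outs are a named input with no stated link to patients, and they overlap with what sites already report. Used in reach, they would make it depend on distribution route and would place downloads in both the outcome and the website engagement predictor.

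The size cannot be fixed from the document. If the counts are added without de-duplication, the assumed cases give 50% to 180%, against 50% to 90% from site-reported patients alone. If accesses serve only as a cross-check outside the calculation, there is no inflation and no shared event, and the remaining task is to say so. The conclusion rests on the text as written and does not depend on the illustrative numbers.

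**What to change.** - Define the numerator once and use it throughout: unique eligible patients to whom the site gave or sent an aid, in any format, during the month, each counted once and taken from the monthly site report.
- Ask for exactly that count in the monthly email.
- Use the same wording in the definition, the label of the data source and the Evaluation text.
- Report downloads and click-outs separately, as a platform-use measure or a cross-check, and state that they do not enter the reach calculation. This also removes the shared event from the regression on website engagement.

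The change costs some wording in the Reach section and the email template. The downside is that reach then rests on site self-report alone, and the reported figure may be lower.
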